### Assessments

2.3

Parents, children older than 8 years and teachers will complete questionnaires online. Parents will also be interviewed by the researcher.

The psychologist-researcher who performs the assessments will be blinded for participants’ allocated intervention. Children and parents, as well as the treatment-staff are explicitly asked not to talk about their randomization condition with the psychologist-researcher. Both groups are treated with the standard treatment protocol for selective mutism.

Assessments will be carried out at the following time points [1]: T1, baseline assessment during intake, before intervention starts [2]; T2, 12 weeks after baseline, either after first 12 weeks of treatment or 12 weeks of waiting list period [3]; T3, after last treatment session. If at any of the assessments or during the waiting list and/or treatment period there is sudden need for immediate intervention (e.g. in the event of a crisis), unblinding will take place to ensure that the participating patient receives the necessary care.

To acquire information from all informants (parents, guardians, teachers, children/adolescents), standardized questionnaires and interviews will be used with adequate psychometric properties, except for the Dutch translation of the SMQ, which will be validated in this study.

In Table 1, all assessments are listed.

**Table 1 tbl1:** Measures per assessment moment.

Instrument	Variable	Assessment moment		
		T1	T2	T3
Primary outcomes				
Selective Mutism Questionnaire (SMQ)	Selective mutism symptoms	P	P	P
Selective Mutism section of Anxiety Disorders Interview Schedule (ADIS-C)	Selective mutism symptoms	P	P	P
Secondary outcomes				
ADIS-C	Anxiety and mood symptoms	P	a	P
Child Behavior Checklist (CBCL)	Behavioral and emotional problems	P	P	P
Teacher Report Form (TRF)	Behavioral and emotional problems	T	T	T
Youth Self Report (YSR)	Behavioral and emotional problems	C	C	C
Self-Perception Profile Child/Adolescent (SPP–C/A)	Self-image	C		C
Child Health Questionnaire (CHQ)	Quality of life	P		P
Predictors				
Adult Self Report (ASR)	Behavioral and emotional problems	P		
EMBU-P	Parenting style	P		
Demographic variables	Demographics	P		
Health care consumption questionnaire	Health care consumption	P		

P: Parents.

T: Teacher.

C: Child.

SMQ: Selective mutism questionnaire.

ADIS-C: Anxiety Disorder Interview Schedule – Children's version.

CBCL: Child Behavior Checklist.

TRF: Teacher Report Form.

YSR: Youth Self Report.

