SPP-C/A: Self-Perception Profile Child/Adolescent.

CHQ: Child Health Questionnaire.

ASR: Adult Self Report.

EMBU-P: Egna Minnen Beträffande Uppfostran – Parent version.

a At T2, only the reported sections of the ADIS-C interview at T1 are assessed.

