### Secondary outcomes

2.5

*Anxiety/mood symptoms*

Interview: The Anxiety Disorders Interview Schedule (ADIS-C) clinical interview is used to obtain information from parents about possible comorbid problems.

Questionnaires: Emotional and behavioral problems will be assessed by the following questionnaires, which have parallel items.

The Child Behavior Checklist (CBCL) [21,22] will be used to obtain standardized parent reports of emotional and behavioral problems in their child. The Youth Self Report (YSR) [21] is the parallel version of the CBCL, but items are formulated in the child form. Children of 11 years and older will complete the YSR.

The Dutch version of the Teacher's Report Form (TRF) [21,22] will be completed by the teacher of the child. The TRF assesses problem behavior (at school). In the CBCL, YSR and TRF questionnaires, a higher score indicates more emotional and/or behavioral problems. In these questionnaires, we are examining the internalizing and externalizing total scales as well as the subscales. The items related to (social) communication will also be examined individually.

*Self-worth image:* The Dutch version of the Self Perception Profile Child/Adolescent [23,24] is completed by children of 8 years and older.

*Quality of life:* The Dutch version of the Child Health Questionnaire (CHQ) [25,26] is used to assess quality of life of the child.

*Predictors*

*Parental psychopathology:* The Adult Self Report (ASR) [27] will be used to screen for parental emotional and behavioral problems.

*Parental parenting styles:* The Egna Minnen Beträffande Uppfostran – Parent version questionnaire (EMBU-P) [28] will be used to assess the parenting style parents use for the child.

*Demographic variables:* Demographic variables such as age, gender, socio-economic status and bilingualism will be assessed during intake, using a semi-structured interview used in care as usual.

*Health care consumption:* Previous physical and mental health consumption will be assessed during intake, using a standardized questionnaire [29].

*Treatment integrity*

To check treatment integrity, all treatment sessions will be audio/video-recorded (if consent of parents and child). Recordings will be saved safely and coded. A random 20% of all sessions will be rated by two independent raters. To avoid protocol drifting, monthly supervision will be given by a certified psychologist. The psychologists providing treatment are trained in the protocol.

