### Intention to treat

3.2

The statistical analyses will be based on the intention-to-treat principle. If appropriate, secondary analyses will be conducted using a per-protocol basis.

Primary and secondary outcomes: Pre-post changes (pretreatment and post treatment assessment of the treatment versus WCG group) on the primary outcome (symptoms of selective mutism) will be tested with repeated measures analyses (factorial repeated measures ANOVA). To determine pre-post change in treatment outcome (responders vs. non-responders) paired sample t-tests will be executed. The effectiveness on secondary outcome measures: symptoms of anxiety/depression, self-image, quality of life and care consumption, will be tested with the same analyses. With linear and logistic regression predictors (e.g., gender, age, socio-economic status, bilingualism, parental psychopathology and parenting styles) for treatment outcome can be determined (p < .05). In the analyses, the number of treatment sessions will be included as a covariate.

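### Three of the four secondary outcomes promised an effectiveness test are not scheduled to allow it: care consumption has no follow-up value, and self-image and quality of life have no untreated comparison

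*Protocol article*

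**What the plan says.** Section 3.2 (Intention to treat) defines the main analysis as "Pre-post changes (pretreatment and post treatment assessment of the treatment versus WCG group", tested by repeated-measures ANOVA. It then names four secondary outcomes, symptoms of anxiety and depression plus three more, and states that "self-image, quality of life and care consumption, will be tested with the same analyses".

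Section 2.3 (Assessments) fixes three time points. T1 is baseline. The second is "T2, 12 weeks after baseline, either after first 12 weeks of treatment or 12 weeks of waiting list period". T3 follows the end of treatment. The same section says that both groups receive the treatment protocol.

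Table 1 gives the schedule by instrument:

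- "Health care consumption questionnaire" stands under Predictors, with an entry at T1 and none later. Section 2.5 agrees: "Previous physical and mental health consumption will be assessed during intake, using a standardized questionnaire".
- "Self-Perception Profile Child/Adolescent (SPP–C/A") and "Child Health Questionnaire (CHQ") have entries at T1 and T3 and none at T2.
- The ADIS-C anxiety and mood sections have full entries at T1 and T3. Footnote a limits the middle one: "At T2, only the reported sections of the ADIS-C interview at T1 are assessed".
- CBCL, TRF and YSR have entries at all three time points.

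**The concern.** In a waiting-list design, the randomised evidence on effectiveness comes from the period in which one arm is treated and the other is not. Here that period ends at T2. An outcome that is not measured at T2 cannot contribute to that comparison, and an outcome measured only at baseline cannot show any effect.

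The stake is how the results would be read. A group-by-time test on SPP or CHQ from T1 to T3 would look like a treatment-versus-control result. A null finding could be taken as no benefit, when both arms may have benefited. A significant time effect could be taken as effectiveness, when it has no untreated comparison. For care consumption, the protocol promises a result that its data cannot produce. An analysis plan cannot repair this, because the values are not scheduled to be collected.

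**Working it through.** No figure in the protocol bears on this point. The check sets section 3.2 against Table 1 and sections 2.3 and 2.5.

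**Step 1. Schedule against promise.**

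| Outcome named in 3.2 | Instrument | T1 | T2 | T3 | Treated-versus-untreated comparison |
|---|---|---|---|---|---|
| Care consumption | Health care consumption questionnaire (a predictor) | yes | no | no | none; no change score exists |
| Self-image | SPP | yes | no | yes | none |
| Quality of life | CHQ | yes | no | yes | none |
| Anxiety/depression | ADIS-C anxiety and mood sections | yes | partial | yes | yes, for sections reported at T1 |
| Anxiety/depression | CBCL, TRF, YSR | yes | yes | yes | yes |

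**Step 2. What a T1-T3 comparison estimates.** Let *g(w)* be the change that would occur without treatment over *w* weeks, and let *τ* be the effect of a completed course. For illustration, assume *τ* is the same whether the course starts at once or after the wait. Section 2.2 gives an average treatment duration of 22 weeks. If waiting-list children start at week 12, their T3 falls on average at 12 + 22 = 34 weeks, against 22 weeks in the treatment arm.

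- Treatment arm, T1-T3: *τ + g(22)*
- Waiting-list arm, T1-T3: *τ + g(34)*
- Group-by-time contrast: [*τ + g(22)*] − [*τ + g(34)*] = *g(22) − g(34)*

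The treatment effect cancels. What remains is the difference in elapsed time. The time effect averaged over the arms is *τ* + [*g(22) + g(34)*]/2, which mixes treatment with natural course.

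**Step 3. The same contrast at T2.** With *τ₁₂* the effect of the first 12 weeks of treatment:

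- Treatment arm, T1-T2: *τ₁₂ + g(12)*
- Waiting-list arm, T1-T2: *g(12)*
- Contrast: *τ₁₂*

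This is the randomised treated-versus-untreated effect. SPP and CHQ are not collected at the time point that yields it.

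**Step 4. ADIS-C at T2.** The sections to be repeated are chosen from T1 data by one rule in both arms. A between-arm comparison of those sections is therefore a valid randomised comparison, and severity within them can rise, stay or fall. What is lost at T2 is any problem that first appears in a section not reported at T1. The number of affected sections cannot increase from T1 to T2 in either arm.

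**Step 5. How much SPP at T2 could deliver.** Section 2.5 gives SPP to children from age 8, and the Inclusion paragraph says that most referred children are younger than that. The share is not given. Assuming 10% to 40% are 8 or older, the number per arm is 38 × 0.10 = 3.8 (about 4) to 38 × 0.40 = 15.2 (about 15). With the protocol's d = 0.58 borrowed for illustration, a two-sample t-test at two-sided 0.05 has power of about 0.11 to 0.34.

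**The case against.** Four arguments can be made for the plan as written.

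- **The self-image and quality-of-life tests can be computed.** T1 and T3 exist in both arms, so the ANOVA and the paired t-tests of section 3.2 will run. This is correct. The defect is the missing untreated comparison, and only care consumption is uncomputable.
- **The T3 weakness is not specific to these instruments.** The sample size paragraph defines the primary outcome itself as the T1-T3 change, so the wider problem lies there. That stands, and the two should be resolved together. There is still a difference: the primary measures are also taken at T2, so they can be re-analysed on T1-T2. SPP and CHQ cannot.
- **Care consumption may be a drafting slip.** This is plausible, since the Discussion also treats previous health care use as a possible moderator. It makes the correction easy, but section 3.2 still promises a test without data.
- **Anxiety and depression are well covered.** CBCL, TRF and YSR fall under the anxiety/mood heading in section 2.5 and are scheduled at T2. This stands in full.

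A reader might infer from footnote a that the T2 ADIS-C score can only stay level or fall, that it is biased in favour of treatment, or that it conceals all worsening on the waiting list. The documents do not support this. Reported sections are reassessed and can worsen, and the selection is made at baseline in the same way in both arms. The footnote does not restrict T3. Only new problems in other sections go unseen at T2.

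**Conclusion.** The point holds for three of the four outcomes named in section 3.2. For care consumption, section 3.2 contradicts Table 1 and section 2.5, and no effect can be computed. For self-image and quality of life, the analysis can be run but does not compare treated with untreated children. For the fourth, anxiety and depression, a randomised T2 comparison exists through CBCL, TRF and YSR; the ADIS-C interview is limited at T2 only in that it misses new problems in sections not reported at T1.

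It would go too far to say that the secondary outcomes as a whole cannot be tested.

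The conclusion on SPP and CHQ rests on section 2.3: both groups are treated, and T3 comes after treatment. The 34-week figure further assumes that waiting-list treatment starts at week 12 and lasts the average 22 weeks. The conclusion does not depend on those exact durations. These are secondary outcomes, so the trial's main question is not affected by this point, but the effectiveness claims for them should not stand as written.

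**What to change.** 1. **Care consumption.** Remove it from the outcome list in section 3.2 and keep it as a predictor. This costs one change of wording.
2. **SPP and CHQ, preferred option.** Add CHQ at T2 for parents, who already complete questionnaires then, and SPP at T2 for children aged 8 and older. Test both on T1-T2. The cost is an amendment and a slightly longer T2 battery. Children aged 8 to 10 would gain a T2 questionnaire where they now have none, because YSR, the only child-completed instrument at T2, starts at age 11. Few children would contribute to SPP, so its result should be presented as imprecise.
3. **SPP and CHQ, if T2 is not extended.** Report their T1-T3 results as uncontrolled pre-post change and withdraw the effectiveness claim for them. This costs only wording and remains possible after recruitment has ended.
4. **ADIS-C anxiety and mood.** Restrict the T2 comorbidity comparison to sections reported at T1, and state that new-onset problems in other sections are not captured at T2. This costs only wording.

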### Intervention

2.2

A standardized, behavioral therapeutic protocol was developed in the Netherlands to treat SM [16]. Children learn in different steps, by using gradual exposure to challenging situations, shaping and modelling. The advantage and innovative aspect of this protocol is that treatment is carried out solely at school. Since at school the problem is present most evidently, a therapist goes to school to practice individually with the child. This helps to generalize the learned exercises to the school situation. Every week the child learns step by step to make sounds and to speak, after which the speaking behavior is extended to various places in school with as the final goal: participating actively in the circle discussion in the classroom.

The protocol is mainly based on behavioral techniques, with as the primary aim stepwise practicing to speak. However, for children from 12 years and older, additional cognitive elements (e.g. helping thoughts) which are used in traditional cognitive behavioral therapy for anxiety [17], are available to be used optionally. The therapist involves the teacher as a co-therapist in the treatment process. After each weekly treatment session at school, the therapist instructs the teacher how profit can be maintained and which exercises to practice during the week. The teacher then continues the exercises throughout the week, finding short moments in time during the week to practice with the child. The therapist is in touch with the teacher face to face after each therapy session, by email or phone when necessary.

Previous clinical experience learns that the average treatment duration with this protocol is 22 weeks.

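### Number of treatment sessions, fixed only after randomisation, is made a covariate in analyses declared intention-to-treat, with no limit on the models it enters

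*Protocol article*

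**What the plan says.** Section 3.2 opens with the principle: "The statistical analyses will be based on the intention-to-treat principle". It then lists a factorial repeated measures ANOVA of treatment against the waiting list control group (WCG), paired t-tests, the same methods for secondary outcomes, and linear and logistic regressions for predictors. It closes with: "In the analyses, the number of treatment sessions will be included as a covariate". It does not say which of these models is meant, or whether the count is sessions up to a given visit or the total delivered.

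Three other places matter:

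- **Assessments (2.3).** T2 is placed at 12 weeks, "either after first 12 weeks of treatment or 12 weeks of waiting list period". The last visit is "T3, after last treatment session". The section adds: "Both groups are treated with the standard treatment protocol for selective mutism".
- **Intervention (2.2).** Sessions are weekly and the child moves in steps towards speaking in class. Length is given only as an average of 22 weeks.
- **Sample size calculation.** The primary contrast is the T1-T3 change, with d = 0.58, two-tailed alpha 0.05, power 0.8 and 38 per group.

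**The concern.** An intention-to-treat comparison may adjust for variables fixed before allocation. Session count is not one of them: it is part of what allocation delivers and may also reflect how the child responds. Holding it constant changes the question from the effect of being assigned to treatment to a contrast at equal dose, and randomisation no longer protects that contrast.

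The stakes differ by contrast. At T3 the risk is bias of unknown size in the primary result. At T2, the only follow-up visit with an untreated arm, the covariate can stand in for arm itself. In the predictor models it can absorb part of the effect of a baseline characteristic if that characteristic makes treatment longer.

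**Working it through.** **The plan's own figure.** For d = 0.58, two-sided 0.05 and power 0.80, the normal formula gives 47 per arm and the t-test 47.6, so 48. The stated 38 matches a one-sided test (37.5). With 38 per arm, two-sided t-test power is 0.70, which is the baseline used below. The mismatch with 80% is a separate matter, and this point does not depend on it.

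**T1-T3, the stated primary contrast.** With two occasions, the arm-by-time test is a test of arm on change. With one session count per child that may also interact with time, it becomes change regressed on arm and sessions. The adjusted arm effect is

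adjusted = d - (within-arm slope of improvement on sessions) × (arm difference in mean sessions).

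Both factors must be non-zero for bias. Assumed, not in the documents: outcome SD 1, session SD 6 around a mean of 22, within-arm correlation ρ between sessions and improvement, and sessions driven by response. The slope is then ρ/6 and the arm difference is 6ρd plus any direct difference δ, so

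adjusted = d(1 - ρ²) - ρδ/6.

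With d = 0.58 and δ = 0:

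| ρ | formula | simulated (3,000 runs, 38 per arm) | simulated power |
|---|---|---|---|
| 0 | 0.58 | 0.58 | 0.70 |
| -0.3 | 0.58 × 0.91 = 0.53 | 0.54 | 0.68 |
| -0.5 | 0.58 × 0.75 = 0.44 | 0.43 | 0.57 |
| -0.7 | 0.58 × 0.51 = 0.30 | 0.30 | 0.42 |

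As a stress case, let the treated arm have 6 fewer sessions (δ = -6). The term -ρδ/6 then equals ρ. With a true effect of zero, the adjusted estimates are -0.3, -0.5 and -0.7, and false rejection is 22%, 60% and 96%. With δ = +6 the shift has the opposite sign, so the direction of bias cannot be known in advance. With ρ = 0, a 6-session difference causes no bias, but power falls from 0.69 to 0.58.

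**T1-T2.** "T2, 12 weeks after baseline, either after first 12 weeks of treatment or 12 weeks of waiting list period" puts the WCG at 0 sessions. Weekly sessions put the treated arm at about 10-12. Let the treated-arm mean be m and its SD s (m = 10-11 and s = 1-3 are assumed). With equal arms, the variance of sessions is m²/4 between arms and s²/2 within, so

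R² = m²/(m² + 2s²), and VIF = (m² + 2s²)/(2s²).

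The unadjusted noncentrality is 0.58 × √19 = 2.53. Dividing by √VIF gives:

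| m, s | VIF | SE multiple | noncentrality | power |
|---|---|---|---|---|
| 11, 1 | 123/2 = 61.5 | 7.8 | 0.32 | 6% |
| 11, 1.5 | 125.5/4.5 = 27.9 | 5.3 | 0.48 | 8% |
| 11, 2 | 129/8 = 16.1 | 4.0 | 0.63 | 9.5% |
| 10, 3 | 118/18 = 6.6 | 2.6 | 0.99 | 16% |

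A simulation with counts capped at 12 gave power of 6-11% when benefit did not vary with dose. When benefit accrued per session, the adjusted arm effect was about 0 (-0.01 to 0.05) instead of 0.58.

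**Predictor models.** Assume difficulty = 0.4x + 0.6u, with x the baseline predictor and u unmeasured, both of SD 1, and sessions proportional to w × difficulty plus noise of SD 0.7. The slope of x after adjusting for sessions is 0.4 × 0.49/(0.49 + 0.36w²). This gives 0.40, 0.38, 0.34 and 0.23 for w = 0, 0.25, 0.5 and 1. A simulation with tighter tracking (w = 1) gave 0.17, which corresponds to session noise of about 0.5: 0.4 × 0.25/(0.25 + 0.36) = 0.16. The plausible range therefore runs from no loss to more than half.

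**The case against.** The strongest reply concerns scope. The sentence directly follows the predictor regressions, and a paired t-test takes no covariate, so the wording cannot literally cover every analysis listed. The authors may have meant only the regressions. That is possible, but the text does not say so, and the sentence stands under the intention-to-treat heading after the between-arm test. The Abstract also describes the second aim as finding baseline predictors, which sessions are not. Adjusting for dose there can be defended as a different question, if it is labelled as one.

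A reader might infer that the covariate wipes out the power of the primary test. The documents do not support that. The collapse belongs to T1-T2 and to a count stopped at T2, while the stated primary contrast is T1-T3, when both arms have been treated and session counts can overlap. If the covariate is total sessions, equal across arms (mean 22, assumed SD 6), VIF is 1.01 and power stays at 0.70 when sessions are unrelated to outcome. If sessions track only the part of the outcome not due to arm (correlation -0.3 or -0.5), the estimate stays at 0.57-0.58 and power is 0.73-0.82. This part of the objection stands.

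It also stands that no passage states that length depends on response. That is inferred from the stepwise goal, the absence of a stated fixed length, and a last visit tied to the end of treatment.

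**Conclusion.** The sentence is wrong as written and should be corrected before analysis. Applied to the treatment-versus-WCG models, it contradicts the declared intention-to-treat principle, whatever the size of the resulting error.

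The size is conditional:

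- **T1-T3:** 0.58 becomes 0.54 to 0.30 for assumed correlations of -0.3 to -0.7. There is no bias if sessions are unrelated to arm and response.
- **T1-T2:** VIF is about 7-62 and power 6-16% against about 70%, only if the covariate is sessions received by T2 and that contrast is tested.
- **Predictor models:** part of a baseline predictor's effect may be absorbed, by an amount that rests wholly on assumptions.

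The documents do not show that the primary test loses its power, that a comparison at equal sessions is impossible at T3, or that response determines treatment length.

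**What to change.** Replace the closing sentence of section 3.2 with a statement that:

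- sessions are not a covariate in the between-arm analyses of primary and secondary outcomes;
- sessions are left out of the main baseline-predictor models;
- the number of sessions is reported descriptively by arm;
- any dose-adjusted or dose-response model is a separate analysis labelled exploratory, with the session count defined (up to which visit, or total).

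The cost is a few lines of text. It needs no extra data, visits or participants.
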